### Face-to-Face Learning

Face-to-face teaching will proceed according to the following steps based on the Peyton approach [14]: (1) the instructor will perform a complete doffing sequence in real time without any comments; (2) the instructor will perform a doffing sequence accompanied by step-by-step explanations (description of key points); (3) the learners will be asked to guide the instructor through the doffing sequence, step by step; (4) the learners will be asked to perform the complete doffing sequence before receiving individualized feedback. Each participant will perform this step only once.

Checklists and “buddy” systems have been used to improve the efficiency and security of doffing sequences [34,35]. Even though such techniques are undoubtedly useful, prehospital providers are required to perform PPE doffing procedures in many different locations, and sometimes lack access to either a “buddy” or even to a checklist. We therefore elected to refrain from giving any support document to the participants.

### Primary Outcome

The primary outcome will be the proportion of doffing sequences correctly performed after knowledge acquisition. Since practices differ from one center to another, we have developed an assessment grid validated by an IPC specialist for the assessment of this outcome (Multimedia Appendix 8). The adequacy of the procedure will be blindly assessed individually by two investigators (a prehospital emergency medicine expert and an IPC specialist) viewing the videos recorded in three-quarter view and using the developed checklist. In case of disagreement, a consensus will be reached by discussion.

### Secondary Outcomes

Seven secondary outcomes will be assessed: time required to teach the technique, time required to perform the doffing procedure, learner satisfaction, proportion of correct computer sequences, confidence in using PPE, and knowledge and skill retention.

The time required to teach the technique using the Peyton approach will be recorded on a paper CRF (Multimedia Appendix 9) by the instructor. Time will be measured from the beginning of step 1 until the last participant has completed the fourth and final step.

The time required to perform the doffing sequence will be recorded (in seconds) by analyzing the recording (measured from the moment the first item is taken off until the moment the learner announces that the procedure has been completed).

Learner satisfaction will be measured using a 5-point Likert scale (not satisfied at all, not satisfied, neutral/undetermined, satisfied, very satisfied).

Computerized doffing sequence accuracy involves reordering the presented sequence in random order in two steps: first in the contaminated zone and then in the noncontaminated zone.

Confidence in the ability to use PPE will also be assessed using a 5-point Likert scale (not confident at all, not confident, neutral/undetermined, confident, very confident).

Knowledge retention will be assessed by reordering the computer sequence once again 4-8 weeks after the first acquisition intervention, whereas skill retention will be assessed in the same way as the primary outcome.

### Blinded Data Collection and Assessment

Some outcomes will be recorded electronically. This will allow for their assessment to be independent from subjective human evaluation. For all other outcomes, assessors will be blinded to participant allocation.

Electronic data will be recorded and securely stored in an encrypted MariaDB database (Version 5.5.5; MariaDB Foundation) hosted on a Swiss server.

At the end of the study, all electronic data will be extracted to a comma-separated value file by the only investigator who will have access to the dataset ([name]). No personal data (name, first name, date of birth, or IP address) will be collected.

### Sample Size

According to two previous studies [12,13], the percentage of correct doffing sequence compliance through the use of the e-learning module should be very low, as no participant was able to recreate the correct sequence on the online platform in either study. However, practical reality might be dissociated from the theoretical answers gathered on online platforms, making a control group necessary in this study. For the record, a recent observational study showed that 90% of the doffing sequences were incorrect [37].

We calculated that 46 participants would be needed to have a 90% chance of detecting, at the 5% significance level, an increase in the primary outcome from 10% in the control group to 50% in the experimental group; additional participants will be accepted as the training will be part of their curriculum.

### Statistical Analysis

Data analysis will be performed using Stata 15.1. Owing to the small sample size, only nonparametric tests will be used. Fisher exact test will be used for dichotomous variables and the Mann-Whitney *U* test will be used for continuous variables. The computerized doffing sequence accuracy will first be analyzed as a whole and then according to the respective doffing zones (contaminated and noncontaminated). This should help determine whether further teaching efforts should be concentrated on a particular part of the sequence. The Likert scales will be described graphically and then dichotomized for statistical analysis (satisfied versus not satisfied; confident versus not confident). The results will be described as a percentage with 95% CI for the proportions and according to the median (Q1-Q3) for the continuous variables. A *P* value <.05 will be considered significant. A subgroup analysis by working status (actively working in an ambulance service or not) will be carried out as an increased rate in adequate choice of PPE has been shown in this subgroup [12]. Missing data will be excluded. There will be no adjustment or imputation.

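### Satisfaction and confidence are tested only after five ordered levels are cut to two; the rank test already in the plan would use the whole scale and is more powerful against a general shift

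*Protocol article*

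**What the plan says.** The Secondary Outcomes section of the protocol article defines satisfaction on five levels ("not satisfied at all, not satisfied, neutral/undetermined, satisfied, very satisfied") and confidence likewise, on a "5-point Likert scale (not confident at all, not confident, neutral/undetermined, confident, very confident". Both are ordered and have a neutral middle level.

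The Statistical Analysis section then states: "The Likert scales will be described graphically and then dichotomized for statistical analysis (satisfied versus not satisfied; confident versus not confident". The tests are assigned by variable type: "Fisher exact test will be used for dichotomous variables and the Mann-Whitney" U test for continuous ones. The two collapsed scales therefore go to Fisher. The general rationale is "Owing to the small sample size, only nonparametric tests will be used", and the threshold is a P "value <.05 will be considered significant". No reason is given for collapsing the scales.

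**The concern.** The plan cites a small sample and then, for two outcomes, discards information that it has collected. Once the five levels are cut, a learner who moves from satisfied to very satisfied, or from the lowest level to the next, contributes nothing to the test. The plan already holds a rank test that needs no cut-point, but reserves it for continuous variables.

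At stake is the chance of detecting a real difference in satisfaction or confidence with 46 to 62 participants. A secondary issue is the label: the negative side of the split carries the same name as a single level of the scale, so the text does not say outright where the neutral answers go.

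**Working it through.** **Inputs from the protocol.** The allocation is 1:1. The Sample Size section gives 46 participants (23 per arm), and Study Design and Setting gives 62 invited students (31 per arm if all take part). The level is 5%, taken as two-sided because the sidedness is not stated. There is no power statement for the Likert outcomes.

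**The plan's own figure.** The 46 belongs to the primary outcome (10% vs 50%, 90% power). The unpooled two-proportion formula reproduces it: (1.960 + 1.282)² × (0.1×0.9 + 0.5×0.5) / 0.4² = 22.33, so 23 per arm. It serves here only to fix the arm size.

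**Assumptions, none of them from the documents.** Three control distributions over the five levels, lowest first:
- A: 5/10/25/40/20%
- B: 2/5/13/45/35%
- C: 10/25/30/25/10%

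The effect is a proportional-odds shift: at every cut, the odds of being at or above it are multiplied by 3. For the top two levels:
- A: 0.60/0.40 = 1.5; ×3 = 4.5; 4.5/5.5 = 82% (from 60%)
- B: 0.80/0.20 = 4; ×3 = 12; 12/13 = 92% (from 80%)
- C: 0.35/0.65 = 0.538; ×3 = 1.615; 1.615/2.615 = 62% (from 35%)

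**Tests compared by simulation.**
- Mann-Whitney on five levels with the tie-corrected variance n₁n₂/12 × [(N+1) − Σ(t³−t)/(N(N−1))], where t is the total count at each level.
- Fisher exact on levels 4–5 against 1–3, that is, with neutral on the negative side.

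| Control | 23/arm: Mann-Whitney | 23/arm: Fisher | 31/arm: Mann-Whitney | 31/arm: Fisher |
|---|---|---|---|---|
| A | 51% | 26% | 64% | 38% |
| B | 49% | 14% | 61% | 16% |
| C | 52% | 34% | 66% | 48% |

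Repeat runs differ by a point or two. With no effect, Mann-Whitney rejects in 4.5–5.2% of trials, so its advantage is not bought with false positives.

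**How much is Fisher and how much is the cut.** An uncorrected chi-square test on the same dichotomy, 31 per arm, separates the two:
- A: 38% (Fisher), 48% (chi-square), 63% (Mann-Whitney in that run). Fisher's conservatism explains (48−38)/(63−38) = 10/25 = 40% of the gap.
- C: 48%, 59%, 66%. Here it explains (59−48)/(66−48) = 11/18, about 60%.

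**Other distributions.** Five further control distributions, with odds ratios 3 and 5 at both arm sizes, all favoured Mann-Whitney. With neutral on the negative side, the smallest gap was 92.6 − 82.3 = 10.3 points. The largest was 88.2 − 15.0 = 73.2 points, for a distribution with 85% already in the top two levels.

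**A different shape of effect.** Let training only move learners from levels 2 and 3 into level 4, leaving both ends unchanged:
- 10/25/30/25/10% to 10/10/10/60/10%: the top two levels go from 35% to 70%. At 31 per arm, Fisher has about 74% and Mann-Whitney 50%; at 23 per arm, 57% and 40%.
- 5/10/35/30/20% to 5/5/5/65/20%: the top two go from 50% to 85%. At 31 per arm, Fisher has 80% and Mann-Whitney about 45%.

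Here the ranking reverses.

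**Place of neutral.** In scenario A at 31 per arm, Fisher's power is 38% with neutral negative, 9% with neutral positive and 23% with neutral dropped.

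**The case against.** The strongest reply is that the ranking of the two tests follows from the assumed effect. A proportional-odds shift suits a rank test, and the documents give no ground for preferring it to an effect concentrated at the cut. This stands: a reader might infer that dichotomizing must cost power in this trial, and the reversal above shows that it need not. It also stands that part of the gap comes from Fisher rather than from the lost ordering.

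Three further inferences are tempting but unsupported:
- **That satisfaction will sit at the top of the scale**, so that the dichotomy has almost no contrast. The documents say nothing of the kind, and the results for B rest on that assumption alone.
- **That a move from satisfied to very satisfied would go unseen.** The scales are to be shown graphically, so it would be visible; only the test ignores it.
- **That the neutral level is left without a side.** The split reads most naturally as satisfied against everything else, which puts neutral on the negative side. The overlap with a level's name is a small ambiguity, of a kind that an article may leave to its fuller documents.

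Nor does the rank test rescue a modest effect: at an odds ratio of 2 and 31 per arm, Mann-Whitney itself reaches only about 29–32%.

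Finally, a percentage satisfied with a 95% CI is a legitimate and readable summary, and Fisher controls the type I error. That supports keeping the percentage as description. It does not explain why the only test should discard the ordering.

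**Conclusion.** The point holds as a conditional one. The protocol commits two ordered five-level outcomes to a two-group test without giving a reason, although a test for ordered data is already in the plan. Under a general shift of odds ratio 3, the cost in the three scenarios is 18 to 35 points of power at 23 per arm (52−34 and 49−14) and 18 to 45 points at 31 per arm (66−48 and 61−16). These figures depend on assumed distributions, on the proportional-odds form and on neutral being counted as negative. They include Fisher's conservatism, and they do not hold if the effect lies only at the cut.

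Two of the seven secondary outcomes are affected. The primary outcome and its conclusion are not. This is a cheap improvement worth making, not a flaw that threatens the trial.

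**What to change.** In the analysis section, state that satisfaction and confidence are compared between groups on all five levels with the Mann-Whitney U test. Keep the graphs, and keep the percentage satisfied or confident with its 95% CI as a descriptive summary, saying in words that neutral counts as not satisfied or not confident.

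The change takes one or two sentences and needs no new data or participants. The article says that the protocol will not be modified once published, so the change should be recorded, with its date, before the coded database is analysed.

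There are two costs: some power is lost if training acts only across the satisfied/not satisfied cut, and the P value no longer corresponds directly to the reported percentage. A version of the rank test stratified by school is not part of this fix; it would be a separate change, and the plan rules out adjustment.

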## Discussion

### Main Considerations

This study should help determine whether face-to-face training using the Peyton 4-step approach in addition to the e-learning module can improve the application of a doffing procedure created by IPC specialists. It should also determine whether this approach improves knowledge and skill retention.

Four learning preference modalities have been previously described [41]: visual, which includes the depiction of information in diagrams, maps, graphs, arrows, circles, hierarchies, and other devices, that people use to represent what could have been presented in words; aural/auditory, which describes a preference for information that is “heard or spoken”; reading/writing, which describes preferences for information displayed as words; and kinesthetic, which refers to the “perceptual preference related to the use of experience and practice (simulated or real).” Although the e-learning module alone might suit the learning preferences of two of the four categories (visual and reading/writing) and face-to-face training may preferentially suit the visual, auditory, and kinesthetic categories, the combination of an e-learning module with face-to-face learning should theoretically suit all four categories.

Concerning our target population, assessment with first-year students who are new to the field and who have not yet been exposed to PPE use will allow us to test our hypothesis on learners who are still naive regarding the doffing method. These students should not be prejudiced and should not have developed any particular habit, good or bad, regarding the use of PPE.

One of the strengths of our study is that the videotapes will be independently assessed by an IPC expert and a prehospital emergency medicine expert.

We chose to design this study to assess the impact of face-to-face learning added to the e-learning module. Another interesting design would be to assess the gain of adding the e-learning module to face-to-face learning with the control group following the face-to-face learning alone and to the experimental group following the face-to-face learning and e-learning module. Although we considered creating a third group to test this hypothesis, we finally decided on the use of two groups given the limited sample size.

### Limitations

Some limitations can already be anticipated. First, the specific population of the sample may limit the generalizability of the results.

Second, using third-year students as instructors allows us to blind instructors, but can limit the quality of teaching. Indeed, these students who will be trained as an instructor within the framework of the study have no expertise in either IPC or in teaching, and have no or little experience in their profession and as an instructor. When peer students or student tutors are used as teachers, the effectiveness of the Peyton teaching approach is less clear [15].

The aim is to teach the technique for the first time, and therefore it will not be integrated in a care simulation and will be performed in a classroom setting. Therefore, the environment will not be representative of the actual situations in which the participants will have to perform these actions. This implies that the mental load on the learners will be lower than when they will have to apply these techniques in the field or integrated into simulations. Therefore, it could be beneficial, after learning the procedure, to train for actual application during simulated care situations.

### Conclusion

This study should help to determine whether face-to-face training in addition to an e-learning module can improve the application of a complex procedure and enhance its retention.

## Appendix

Multimedia Appendix 1 SPIRIT checklist.

Multimedia Appendix 2 PPE doffing procedure for instructors.

Multimedia Appendix 3 Peyton approach stages reminder sheet for instructors.

Multimedia Appendix 4 Copy of email to participants.

Multimedia Appendix 5 Questionnaire 1: demographic data.

Multimedia Appendix 6 VARK paper case report form (CRF).

Multimedia Appendix 7 SPIRIT diagram. Timeline of enrollment, interventions, and assessments.

Multimedia Appendix 8 Assessment grid.

Multimedia Appendix 9 Instructors paper case report form (CRF).

## Abbreviations

CRF: case report form
e-learning: electronic learning
IPC: infection prevention and control
PPE: personal protective equipment
VARK: visual, aural, reading/writing, or kinesthetic
